#### Step rate

2.14.11

Step rate during running will be recorded using Garmin running watch that support the measurement of wrist‐based running dynamics. Measurements of step rate with Garmin running watches have been shown to be valid and reliable (ICC = 0.931) [26]. In addition, participants' running step rate will be manually counted and recorded over four separate 30‐s intervals during follow‐up sessions. Step rate will be recorded as number of steps per minute.

#### Step length

2.14.12

Step length during running will be calculated from running step rate data provided from each participants Garmin running watch using the following equation: *velocity (m/min) ÷ step rate*.

$$Step\;length\;\left(m\right)=\frac{Run\;speed\;\left(m/\min\right)}{Step\;rate\;\left(steps/\min\right)}$$

Data will be recorded throughout the trial, and measurements recorded and correlated to 2D video footage at baseline, one, two, four and 8 weeks. Step length will be recorded in metres.

### EVALUATION OF INTERVENTION ADHERENCE

2.15

Adherence to interventions and training load will be documented throughout the trial. Participants will be required to record their adherence to the strength program, symptom management advice, response to their run sessions, and run volume via a custom‐built software (The Injury Clinic Pty Ltd., Geelong, Australia) installed on their phone. Adherence to a reduction in running step length will be confirmed at sessions 1 to 5, and the step rate required to achieve the target step length will be recorded by the Garmin running watch for each run. Adherence will be considered to be acceptable if participants in both the intervention and control groups complete 80% of their programmed strength sessions, and if participants in the intervention group complete 80% of their running retraining sessions [27]. Participants strength program will be considered complete if a minimum of 8 out of 12 exercises have been completed within each session.

### Adverse events

2.16

Complications and adverse events associated with the intervention will be recorded in participant files and reported in the final manuscript. Participants will be asked to document the type of adverse event, the body location, the frequency and/or severity of the event. An adverse event will be considered any harmful or unpleasant outcome for which there is a known or plausible association with the interventions and those for which there is none [28].

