Previous studies investigating running retraining to reduce tibial loads have found real‐time visual feedback [29, 30], haptic feedback [33], and clinician verbal feedback [29] are all effective in reducing tibial loads. Whilst these studies have demonstrated that running retraining can be effective in reducing tibial loads, none have examined the clinical effectiveness of running retraining among runners with MTSS. In addition, there is an absence of studies investigating the effects of running retraining on tibial loads beyond immediate effects. Despite this, running retraining is a common strategy adopted by clinicians and coaches in the management of running related lower‐leg pain [3]. With few running retraining trials conducted for running‐related injuries, the expected rates and types of adverse events remain somewhat unknown. However, as the cue to reduce step length will likely result in minimal changes to other gait parameters [4] the risk of adverse events is considered negligible.

Whilst ‘best standard care’ for MTSS has not yet been established, a clinical trial by Mendez‐Rebolledo and colleagues found that the inclusion of 6 weeks of neuromuscular training (plyometric and weightbearing drills) in uninjured female athletes reduced the incidence of MTSS [34]. To our knowledge, the effect of a strength training program inclusive of plyometric exercises on runners with MTSS has yet to be investigated. The inclusion of ‘best standard care’ as a comparator intervention assists with accounting for non‐intervention effects (e.g., placebo effect, Hawthorne effect, natural resolution, etc.) not directly related to the running retraining intervention. Providing participants with an intervention that they perceive as being equally credible and expected to provide similar benefits as the experimental intervention will assist in minimising confounding factors such as resentful demoralisation among participants not receiving the running retraining. As all participants will spend a similar amount of time with clinicians, receive the same number of appointments, their experience in the trial is expected to be very similar (with the only exception being the inclusion of running retraining).

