This trial has been designed to optimise its scientific rigour while ensuring a high clinical utility. Some strengths of the trial include the use of allocation concealment, blinded data entry, adhering to the intention‐to‐treat principle to analyse data, and the use of a comparator intervention as a control. In addition, this trial has been designed to have high external validity, with the eligibility criteria being representative of a demographic most likely to experience MTSS, and the study being conducted in a real‐world setting, ensuring any findings regarding the success of interventions can be transferable to clinical practice. If effective, the gait retraining program's use of a commercially available wearable device ensures that our findings will be reproducible and will translate readily to clinical settings. However, due to the nature of the interventions, inherent limitations with this trial are a lack of blinding of the primary investigator and blinding of participants via limited disclosure. We acknowledge the potential for clinician bias, and plan to address this by ensuring a similar amount of time is spent with each participant, that the duration of each data collection session be recorded to allow a comparison at the conclusion of the trial, and that an assessor blinded to group allocation be involved in all decision making regarding best standard care and progression of load. Accordingly, the findings of this trial will need to be viewed in consideration of its strengths and limitations.

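### Section 2.16 records and reports adverse events associated with the intervention, but its own definition of an adverse event includes events with no association

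*Protocol article*

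**What the plan says.** Section 2.16 (Adverse events) has three sentences.

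- The first sets what is kept and published: "Complications and adverse events associated with the intervention will be recorded in participant files", with the final manuscript named as the place where they are reported.
- The second sets what participants supply: "Participants will be asked to document the type of adverse event, the body location, the frequency and/or severity of the event". It has no condition about cause.
- The third defines an adverse event as "any harmful or unpleasant outcome for which there is a known or plausible association with the interventions and those for which there is none".

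Two statements in section 4 (Discussion) bear on this. The authors say that, with few retraining trials done, "the expected rates and types of adverse events remain somewhat unknown", although they then judge the risk from the cue to be negligible. They also acknowledge that "inherent limitations with this trial are a lack of blinding of the primary investigator".

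**The concern.** The first sentence carries a qualifier about association that the definition expressly removes. An unrelated event is an adverse event under the third sentence but lies outside the first.

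If the qualifier is applied, somebody has to decide on causality before an event is entered or published, and the article does not say who. Attribution made with knowledge of allocation can differ between arms, and the reported harms then reflect the attribution as well as the events. An event that was never recorded cannot be recovered at analysis.

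Harm is a live question here. Under section 2.6.1, runners with painful shins in both groups progress weekly running volume by 10% to 30% after the first two weeks, and the authors themselves describe adverse-event rates as not well known.

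**Working it through.** The article gives no adverse-event figure to reproduce. The check is a comparison of wording, followed by an illustration on assumed values.

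**Step 1. Scope of each sentence in section 2.16.**

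| Sentence | Function | Condition on cause |
|---|---|---|
| First | Recording and reporting | Associated with 'the intervention' (singular) |
| Second | Participant documentation | None |
| Third | Definition | Related to 'the interventions' (plural), "and those for which there is none" |

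**Step 2. Does the definition resolve the conflict?** Put the definition in place of the defined term in the first sentence. It then covers any harmful or unpleasant outcome, related or not, that is associated with the intervention. The qualifier is still there and still removes the unrelated events, so reading the definition into the first sentence does not reconcile the two.

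**Step 3. What does 'the intervention' mean?** Sections 2.1 and 2.5 call the retraining arm the intervention group and the other arm the control group, which supports retraining alone. The heading of section 2.5 covers both arms, section 2.9 speaks of every participant being allocated to their intervention, and the Discussion calls best standard care a comparator intervention. These support either treatment. Both readings are open.

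**Step 4. What could attribution-based recording do?** Inputs: 32 per group (section 2.4). The true risks and attribution probabilities are assumptions.

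Expected participants with a recorded event = 32 × true risk × probability that the event is attributed.

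Recorded risk difference = (true risk × attribution) in the retraining arm minus the same product in the control arm.

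With a true risk of 20% in both arms (true difference 0):

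- All events recorded: 32 × 0.20 = 6.4 against 6.4; difference 0.
- Attribution 70% retraining, 30% control: 32 × 0.20 × 0.70 = 4.5 against 32 × 0.20 × 0.30 = 1.9; difference 0.14 − 0.06 = +8 points. Reversing the attribution gives −8 points.
- Attribution 50% retraining, no control event eligible (the retraining-alone reading): 32 × 0.20 × 0.50 = 3.2 against 0; difference +10 points.
- Attribution 50% in both arms: 3.2 against 3.2; difference 0.

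With a true risk of 30% in both arms, the second and third cases become ±12 points (0.21 − 0.09) and +15 points (0.15 − 0).

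With true risks of 30% against 15% and 50% attribution in both arms, the true difference of 15 points is recorded as 0.15 − 0.075 = 7.5 points.

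Differential attribution can therefore create a difference of either sign. Equal attribution leaves a true zero at zero but dilutes a real difference.

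**The case against.** The best defence is that the authors mean to capture everything. The text never says that unrelated events are left out. An explicit definition normally governs a loose introductory phrase, and the second sentence asks participants, who are blinded by limited disclosure, to document events whatever the cause. The article does not say that the unblinded investigator screens events. This stands as far as intent goes: a reader might infer that only related events will be recorded, or that the investigator certainly filters them, and the document establishes neither. It does not rescue the first sentence, which would then misstate the plan and need the same correction.

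A reader might also infer that no control-arm event can qualify. That is the extreme resolution of an ambiguous term, and several sections treat best standard care as an intervention too. Figures with zero events in the control arm are therefore worst cases.

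Three further points limit the consequence:

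- No formal between-group test of adverse events is stated. Section 3.1 lists participant characteristics and the primary and secondary outcomes, and section 2.16 promises reporting only. What is at risk is the set of harms reported by arm.
- Symptom worsening is partly captured in both arms without attribution, through worst pain during a run (2.14.4), reported exacerbations (2.6.1), logged response to run sessions (2.15) and the global rating of change (2.14.2). This softens the problem but does not replace adverse-event reporting.
- Detailed procedures for eliciting events and judging relatedness are matters that a condensed article may leave to the full protocol. Their absence is not criticised here.

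**Conclusion.** The internal inconsistency in section 2.16 is established from the text alone and needs no assumption. That harms reported by arm could be biased is conditional: it requires that the first sentence is applied as written and, for a spurious difference to appear when true risks are equal, that attribution differs between arms. An unblinded primary investigator and an ambiguous reference to 'the intervention' make differential attribution plausible. The safeguards against clinician bias listed in the Discussion (similar contact time, recorded session length, and a blinded assessor involved in decisions on standard care and load) do not mention adverse-event attribution.

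Size and direction cannot be derived from the document. The distortions of 8 to 15 points in the working rest wholly on assumed risks and attribution rates and show only what is possible. It would go too far to say that the safety results will be wrong. The wording should be corrected because it opens an avoidable route to bias and is very easy to close.

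**What to change.** In section 2.16, and in the full protocol if it carries the same sentence, delete the words that tie recording to association with the intervention. State instead that all adverse events in both groups will be recorded regardless of suspected cause and reported by group. If relatedness is to be judged, say that this happens separately and after recording, preferably by the assessor already blinded to allocation (section 2.1 and the Discussion). The existing definition can stay as it is.

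The cost is one reworded sentence and slightly more events to list. Both groups already attend the same five sessions (section 2.8), so no visit is added, and nothing in the treatment of participants changes.

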## DATA ANALYSIS

3

### Descriptive analysis

3.1

Differences between the control and intervention group in demographic and clinical characteristics and for the primary and secondary outcome measures (2, 4, and 8 weeks) will be described and assessed using *t* tests for continuous and chi‐square for categorical variables. If after assessment of the assumptions of the *t* test (such as the homogeneity of variance) are violated, we will use alternatives such as the Welch's test with Satterhwaite approximation as a sensitivity analysis. For cell counts <5, *p* values from chi‐square tests will not be reported.

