**Methods:**

This study is an assessor‐blinded and participant‐blinded, parallel‐group, randomised controlled trial. The trial will recruit 64 participants aged between 18 and 45 years, with a clinical diagnosis of MTSS that has affected their running participation for at least four weeks. Participants will be randomised to receive best standard care (control) or running retraining and best standard care (intervention group) over an 8‐week period. Best standard care will consist of load management advice, symptom management advice, footwear advice and a strengthening program. Running retraining will consist of a cue to reduce running step length. Outcomes will be measured at weeks 1, 2, 4 and 8. The primary outcome measure will be the University of Wisconsin Running Injury and Recovery Index at week 4. Secondary outcome measures include: (i) Exercise Induced Leg Pain Questionnaire—British Version, (ii) global rating of change scale, (iii) worst pain experienced during a run, (iv) weekly run volume, (v) reactive strength index score, (vi) single leg hop test, (vii) soleus single leg maximum voluntary isometric contraction, (viii) gastrocnemius single leg maximum voluntary isometric contraction, (ix) single leg plantar flexor endurance test, (x) running step length, and (xi) running step rate. Data will be analysed using the intention‐to‐treat principle.

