### Sample size

2.4

Sample size was calculated based on the primary outcome measure, the University of Wisconsin Running Injury and Recovery Index (UWRI) [12]. Using a power of 80%, previously reported standard deviation of 6.7 [13], medium effect size (Cohen's *d* = 0.75) of 5 points on the 36‐point UWRI [14] and a significance level set at *α* < 0.05, we estimated using GPower 3.1 (Kiel University, Germany) that a total of 60 participants (i.e., approximately 30 per group) will be required. When estimating sample size we were limited with data available and have opted to use the medium effect size for our estimation. To allow for any imprecision in these estimates, we will have a recruitment target of 32 participants per group.

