### Outcome measures

2.14

The primary outcome measure will be the University of Wisconsin Running Injury and Recovery Index (UWRI). The UWRI is a nine‐item running specific patient‐reported outcome measure that relates to both running progression and symptom surveillance. It has been found to have acceptable internal consistency (*α* = 0.82) and test–retest reliability (ICC: 0.93) when assessing running ability following a running‐related injury [12]. Scores range from 0 to 36.

The secondary outcome measures will be as follows.

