### Mixed effects analysis

3.2

A mixed effects model will be used to assess the mean differences between the groups for the outcomes considered. The fixed effects are between‐participant variables such as age, sex, BMI, symptom management and footwear. These models incorporate time as the random effects which is a within‐subject variable. All assumptions for mixed effects modelling will be checked. As most of the outcome measures will be considered as continuous, normality and homogeneity of variance assumptions will be assessed. If these assumptions are violated, alternative modelling approaches will be considered. Effect modification by age, BMI and sex will be explored using likelihood ratio tests, taking into consideration the sample sizes of the subgroups. Strata‐specific results will be reported if the *p* value for the interaction terms is < 0.1, and if at least one of the observed associations from the strata‐specific models are statistically significant at *p* ≤ 0.05. Results from these models will be presented as estimated effect sizes (both unadjusted and adjusted), standard errors, 95% confidence intervals and *p* values. All statistical analyses will be performed using the latest version of Stata (StataCorp, College Station,TX, USA).

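### The primary outcome is tested by week-4 t test and by unadjusted and adjusted mixed models, and the plan does not say which result decides the trial

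*Protocol article*

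**What the plan says.** The Methods part of the abstract names the time point: "The primary outcome measure will be the University of Wisconsin Running Injury and Recovery Index at week 4". Section 2.14 (Outcome measures) names the instrument only, "The primary outcome measure will be the University of Wisconsin Running Injury and Recovery Index (UWRI", and gives no visit.

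Section 3.1, headed as descriptive, states that differences between the groups "for the primary and secondary outcome measures (2, 4, and 8 weeks) will be described and assessed using *t* tests for continuous" variables. It also plans a Welch-type alternative as a sensitivity analysis.

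Section 3.2 then says: "A mixed effects model will be used to assess the mean differences between the groups for the outcomes considered". It lists age, sex, BMI, symptom management and footwear as examples of fixed effects and treats time as a random effect. It gives no group-by-visit term and no week-4 contrast. On reporting it says: "Results from these models will be presented as estimated effect sizes (both unadjusted and adjusted), standard errors, 95% confidence intervals and *p* values".

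Section 2.4 sizes the trial on UWRI with "a significance level set at *α* < 0.05" and a two-group comparison of means.

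**The concern.** UWRI will have three t tests and at least two model-based p values. The sections point in different directions about which one counts. The sample size in section 2.4 is that of a two-sample t test. The heading of 3.1 suggests that the t tests only describe, yet its text checks test assumptions and adds a sensitivity analysis, as one does for an inferential test. Section 3.2 reads like the main analysis, but its model as written carries no week-4 contrast, so its group effect need not be the primary outcome that the abstract defines.

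If the deciding result is settled only once the results are known, the 5% level no longer describes the decision. The same data could also support opposite conclusions depending on which result is put forward.

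**Working it through.** **1. The plan's own figure.** Inputs from section 2.4: difference 5 points, SD 6.7, power 80%, alpha 0.05. d = 5/6.7 = 0.746. A two-sided two-sample t test (noncentral t) needs 30 per group, 60 in total, with power 81.1%. This reproduces the stated 60. A one-sided test by the normal approximation would need 23 per group, so the 5% level is evidently two-sided. At the target of 32 per group the power is 83.6%. The design therefore rests on one two-group comparison of means.

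**2. False-positive chance under no effect.** Simulation with 32 per group, visits at weeks 2, 4 and 8, equal correlation between visits, complete data, five covariates, and 6,000 trials per row. Correlation and variance explained are not in the document; they are assumed, and the range is shown. For complete, balanced data the visit-averaged model result is the group difference in each participant's mean over visits.

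- A: week-4 t test alone.
- B: week-4 t test or covariate-adjusted week-4 estimate below 0.05.
- C: week-4 t test, or unadjusted or adjusted visit-averaged model, below 0.05.
- D: any of five (t tests at weeks 2, 4 and 8, and both visit-averaged model results).

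| Correlation | Variance explained | A | B | C | D |
|---|---|---|---|---|---|
| 0.3 | 10% | 4.9% | 6.7% | 9.8% | 15.8% |
| 0.3 | 25% | 5.2% | 7.9% | 11.3% | 16.5% |
| 0.5 | 10% | 4.6% | 6.2% | 9.3% | 14.3% |
| 0.5 | 25% | 4.5% | 7.1% | 9.5% | 13.9% |
| 0.7 | 10% | 4.7% | 6.6% | 8.3% | 11.5% |
| 0.7 | 25% | 5.1% | 7.5% | 10.0% | 13.5% |

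The Monte Carlo standard error near 9% is √(0.09 × 0.91/6000) = 0.4 percentage points. Runs of 40,000 trials over the same ranges put C at 8.8 to 10.9%. In round terms B is 6 to 8%, C is 9 to 11% and D is 12 to 17%.

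As a ceiling check, three independent tests would give 1 − 0.95³ = 14.3%. The correlated t tests at the three visits give 10.3 to 13.8% in these runs, below that ceiling.

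**3. Disagreement when the treatment works as designed.** With a true difference of 0.746 SD at every visit and the same ranges, the week-4 t test and the two visit-averaged model results are not all on the same side of 0.05 in about 14 to 18% of trials. If the model targets week 4, the t test and the adjusted estimate disagree in about 8 to 11%.

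**The case against.** The strongest reply is scope. This is a condensed article, and the primary model, contrast and covariates are often left to an analysis plan, which is not shown here. That limits the weight of the point: such a plan may already name one analysis. It does not remove the point, because the article is not silent. It prescribes several tests of the primary outcome side by side, and one of them, as written, does not estimate the outcome that the abstract names.

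The second reply is that the headings imply an order, with 3.1 describing and 3.2 inferring. That reading is available and probably intended. But 3.1 says that outcomes are assessed by t tests, and even on this reading 3.2 leaves the unadjusted and adjusted results on an equal footing.

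A reader might infer that the false-positive chance is two to three times 5%. The documents do not support this as the headline. Its upper part requires the week-2 and week-8 tests to count as primary, and the abstract fixes week 4. A reader might also infer that the investigators intend to claim benefit on any p value below 0.05. No such rule is stated; the reporting sentence in 3.2 concerns presentation. The percentages show what the open choice permits, not what anyone plans to do.

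Disagreement in about a third of trials can be shown, but only at an effect of 0.5 SD, where the week-4 t test has about 50% power. At the effect the trial was designed for, it is about half that.

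Sizing a trial on a t test and analysing it with a mixed model is conventional, and is not a fault here.

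**Conclusion.** The point holds in a limited form. The week-4 time point stands in the abstract but is not carried into sections 2.14 and 3. Several tests of UWRI are prescribed, and none is named as deciding. With week 4 respected, the open choice raises the false-positive chance from 5% to about 9 to 11% (9/5 = 1.8 to 11/5 = 2.2 times) if the model result is averaged over visits, and to about 6 to 8% (1.2 to 1.6 times) if it targets week 4. It reaches about 12 to 17% only if week 2 or week 8 could also carry the claim, which the abstract does not allow. All of this supposes that any one of the listed results could be put forward, and it rests on the correlation, variance explained and complete data assumed above. The disagreement figure of 14 to 18% further assumes the same effect at every visit. The matter merits correction, but it does not call the design into question.

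**What to change.** - In sections 2.14 and 3, repeat that the primary outcome is UWRI at week 4.
- In section 3.2, name one deciding test: the two-sided 5% test of the between-group difference in UWRI at week 4, from one mixed model with a group-by-visit term.
- Replace the open list of covariates with a closed one, restricted to values measured at baseline. Sections 2.6.2 and 2.6.3 show that medicine use is documented, and footwear may be replaced, during the trial. Adjusting for values taken after randomisation would bring a new problem into the deciding test.
- Label the unadjusted model and the week-4 t test as sensitivity analyses, and UWRI at weeks 2 and 8 as secondary.
- Keep section 3.1 descriptive, without between-group p values for outcomes.

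This is wording only, to be settled before unblinding, with no extra data or participants. The price is that a favourable result from a non-primary analysis can no longer carry the conclusion.

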### Study design

2.1

The RUNMETRES (RUNning retraining for MEdial Tibial tRESs) study is a parallel‐group randomised controlled trial conducted over an 8‐week period. Participants will be randomised to a control group (best standard care) or an intervention group (best standard care and running retraining). To ensure allocation concealment, permuted block randomisation with random block sizes, stratified by sex at birth will be undertaken using www.sealedenvelope.com. The investigator responsible for recording the outcome measures will be blinded to participants' group allocation. Participants will be blinded to their treatment allocation via limited disclosure, and precautions will be taken to ensure they are unaware of the other treatment group. The trial has been registered on the Australian New Zealand Clinical Trials Registry (ACTRN12624000230550). The findings from the trial will be reported according to the Consolidated Standards of Reporting Trials (CONSORT) statement [6, 7] and the Template for Intervention Description and Replication checklist [8].

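### Randomisation is stratified by sex, but the outcome t tests and the unadjusted model estimates leave sex out, and no result that includes it is named as primary

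*Protocol article*

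**What the plan says.** Section 2.1 (Study design) uses permuted blocks of random size, "stratified by sex at birth will be undertaken using" an online service. Sex is the only stratification factor.

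The analysis then gives three sets of between-group results:

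- **Section 3.1 (Descriptive analysis).** Group differences in baseline characteristics and "for the primary and secondary outcome measures (2, 4, and 8 weeks) will be described and assessed using" t tests for continuous variables and chi-square tests for categorical ones. Welch's test is the fallback. No covariate enters.
- **Section 3.2 (Mixed effects analysis), unadjusted.** "A mixed effects model will be used to assess the mean differences between the groups for the outcomes considered". Its results are "presented as estimated effect sizes (both unadjusted and adjusted". The article does not define the unadjusted version; by its label it has no covariates.
- **Section 3.2, adjusted.** The fixed effects are "variables such as age, sex, BMI, symptom management and footwear". This is the only place where sex enters a comparison of the groups as a covariate.

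The Abstract fixes the primary outcome and time point (UWRI at week 4). No section says which of the three results is the primary analysis of it.

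**The concern.** Stratifying on sex makes the arms nearly identical in their sex mix. Any difference in outcome between the sexes then drops out of the true sampling error of the group difference. A two-sample t test does not know this. It pools both sexes into one residual variance, so the between-sex part stays in the estimated standard error. If sex is prognostic, the confidence interval is wider than it should be, the real type I error falls below 5%, and precision that the design has already secured goes unused.

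Two of the three stated sets of results have this property. Because none is designated primary, a result that does not follow the randomisation could end up being read as the main one.

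**Working it through.** **Inputs from section 2.4 (Sample size).** A "previously reported standard deviation of 6.7", a difference of 5 points, 80% power, alpha 0.05, 60 participants required and 32 per arm recruited. The article does not say whether the test is two-sided.

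**Step 1: reproduce the stated sample size.** d = 5/6.7 = 0.746. A two-sample t test with two-sided alpha 0.05 and 80% power (noncentral t) needs 29.18 per arm, rounded up to 30, or 60 in total. This matches. A one-sided test would need 23 per arm (46) and does not match. The sample size is therefore already that of a t test without covariates. Its power is 81.1% at 30 per arm and 83.6% at 32.

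**Step 2: effect of leaving out the stratification factor.** Let R² be the share of outcome variance explained by sex. The article gives no value, so a range is shown. Assume equal numbers of each sex, exactly 16 per arm within each sex, and a total SD of 6.7.

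- Standard error that the t test estimates: about 6.7 × √(2/32) = 1.675.
- True standard error under the stratified design: 1.675 × √(1 − R²).
- Excess width: 1/√(1 − R²) − 1.
- Sex gap implied by R²: 2 × 6.7 × √R².

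For R² = 0.05, the true standard error is 1.675 × √0.95 = 1.633 and the excess is 1/√0.95 − 1 = 2.6%. For R² = 0.10, they are 1.675 × √0.90 = 1.589 and 5.4%.

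**Step 3: power and type I error.** 40,000 simulated trials per row, true difference 5 (power) or 0 (type I error), comparing the t test with a linear model on group and sex:

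| R² (assumed) | Sex gap, points | SE too wide by | Power, t test | Power, with sex | Type I error, t test |
|---|---|---|---|---|---|
| 0 | 0 | 0% | 83.5% | 83.5% | 4.8% |
| 0.01 | 1.3 | 0.5% | 83.6% | 83.8% | 4.7% |
| 0.05 | 3.0 | 2.6% | 84.0% | 85.2% | 4.2% |
| 0.10 | 4.2 | 5.4% | 84.6% | 87.0% | 3.7% |
| 0.25 | 6.7 | 15.5% | 86.5% | 92.2% | 2.2% |

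With sex in the model, the simulated type I error is 4.8% in every row.

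**Step 4: check on the simulation.** The Monte Carlo standard error is about √(0.85 × 0.15/40,000) = 0.18 points for power and √(0.05 × 0.95/40,000) = 0.11 points for type I error. All rows reuse one random seed, so the shortfall from 5% in the first row is chance that the other rows share. Direct calculation used the noncentral t with 61 degrees of freedom and noncentrality 5/(true SE) for the model. For the t test it used a normal difference with the true SE, integrated over a noncentral chi-square for the pooled sum of squares (62 degrees of freedom, noncentrality 64 × R²/(1 − R²)). This gives power of 84.2% v 85.4% at R² = 0.05 and 84.8% v 87.2% at 0.10, with t test type I errors of 4.4% and 3.9%. The gaps are the same to within rounding: about 1.2 and 2.4 points.

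**The case against.** The strongest reply is that the plan already uses the stratification factor. The mixed model is the stated tool for group differences and names sex as a fixed effect, while the t tests sit under a descriptive heading beside the baseline comparisons. This stands in large part: it would be wrong to infer that the plan ignores sex. It does not remove the point. Section 3.1 applies inferential tests, with a Welch fallback, to the primary outcome, and the sample size is that of such a test. A reader could fairly take either result as the main one.

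A second reply is that covariate detail, including what unadjusted means, may be in a fuller plan that is not shown. That is fair for the unadjusted model, where the omission of sex is read from the label. It does not cover the t tests, whose form, outcomes and time points the article states.

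A reader might also infer that the trial loses planned power. It does not. The sample size assumed no covariates, and t test power at 32 per arm is at least 83.5% in every row above. What is forgone is extra power, and only if sex is prognostic.

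Finally, a reader might expect the effect to be largest for strength, hop, step length or run volume. That is possible, but the article gives no data on it. The isometric strength measures are already scaled per kilogram and the hop score is a ratio. The calculation covers the UWRI only.

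**Conclusion.** The point holds as a minor one. The t tests in section 3.1 and, by their label, the unadjusted estimates in section 3.2 do not follow the stratified randomisation. Only the adjusted model does, and it is not named as primary.

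The consequence is conditional on sex predicting the outcome. For the UWRI, including sex would gain about 1 power point or less if sex explains up to 5% of the variance, and about 2.4 points at 10%. The 10% case needs a sex gap of 4.2 points, not far below the 5-point treatment effect, and nothing in the article supports a gap that large. Any error is conservative: the type I error stays below 5%, and the group difference is not biased.

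These sizes assume a two-sided test, an even sex split and exact balance within sex. An uneven split or incomplete blocks would make the effect of a given sex gap smaller.

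**What to change.** Three edits to sections 3.1 and 3.2:

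1. In 3.1, replace the outcome t tests with a linear model on group and sex, or keep the outcome comparisons purely descriptive, without p values.
2. In 3.2, define the unadjusted mixed model as adjusted for the stratification factor (sex at birth) only. The adjusted model then adds the other covariates.
3. Name the sex-adjusted between-group contrast in UWRI at week 4 as the primary result.

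Sex is known for every participant at randomisation, so no new data are needed and the sample size is unchanged. The cost is one degree of freedom. If sex turns out to be unrelated to the outcome, power is unaffected to the precision shown (83.5% either way).
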